## Abstract

**Background:**

The optimal duration of dual antiplatelet therapy (DAPT) for patients with coronary multi‐vessel disease (MVD) who have received drug‐eluting stents (DES) remains unclear.

**Hypothesis and Methods:**

The Dual Antiplatelet Therapy in Patients with Coronary Multi‐Vessel Disease (DAPT‐MVD) study is a multicenter, open‐label, randomized controlled trial designed to assess the efficacy and safety of extended DAPT in MVD patients 12 months following DES implantation. We plan to enroll 8250 patients across approximately 100 sites in China. Participants will be randomized in a 1:1 ratio to receive either extended DAPT (75 mg clopidogrel plus 75–150 mg aspirin daily) or monotherapy (75–150 mg aspirin daily) beyond 12 months post‐DES implantation. The follow‐up period will last at least 12 months, with all potential endpoints adjudicated by a blinded Clinical Events Committee. The primary endpoint is major adverse cardiovascular and cerebrovascular events (MACCE), including cardiovascular death, nonfatal myocardial infarction, or nonfatal stroke.

**Results:**

As of April 2024, a total of 8250 participants have been enrolled in the study. The mean age of the enrolled patients was 60.5 ± 8.8years, with 5753 (69.7%) being men.

**Conclusions:**

The DAPT‐MVD study is the first large‐scale trial to evaluate the efficacy and safety of prolonged DAPT with clopidogrel plus aspirin beyond 12 months after DES implantation in MVD patients. The trial will provide novel insights into the optimal duration of DAPT for MVD patients (ClinicalTrials. gov ID: NCT04624854. Registered on 10/27/2020).

## Introduction

1

The World Health Organization reported that 9 million people died of cardiovascular disease worldwide in 2019, accounting for 16% of the total deaths [1]. Aside from patients with single‐vessel disease, approximately 40%–65% of patients with coronary artery disease (CAD) are diagnosed with multivessel disease (MVD) [2, 3, 4, 5].

Compared to those with single‐vessel disease, patients with MVD have a more severe state of atherosclerosis in the vascular bed and tend to have worse clinical outcomes manifested as a higher cumulative incidence of recurrent atherothrombotic coronary events, revascularization, and adverse mortality [5, 6, 7]. With the increasingly widespread use of percutaneous coronary intervention (PCI) in the treatment of CVD, culprit vessels in MVD patients were effectively treated [8, 9].

Dual antiplatelet therapy (DAPT) with aspirin and an adenosine diphosphate (ADP) receptor blocker has been established as a standard therapy to prevent thrombotic arterial vessel occlusion after PCI [10]. Abundant evidence from clinical trials demonstrated a significant reduction in the risk of major adverse cardiovascular and cerebrovascular events (MACCEs) for 1 year with DAPT treatment relative to aspirin monotherapy following drug‐eluting stent (DES) implantation [11, 12, 13]. However, the duration of antithrombotic therapy for patients with MVD after PCI is still controversial.

The previous randomized controlled trial (RCT), PEGASUS‐TIMI 54, showed a dramatic reduction in the risk of MACCEs in patients with prior myocardial infarction (MI) and MVD treated with prolonged DAPT treatment (60 mg and 90 mg ticagrelor twice daily in patients treated with low dose aspirin) [14]. In consideration of the higher risk of bleeding due to the potent antiplatelet effect of ticagrelor, clopidogrel, another P2Y12 receptor inhibitor, can reduce net adverse clinical and cerebral events (NACCEs) and bleeding events compared with ticagrelor in a real‐world study [14, 15, 16]. Therefore, clopidogrel‐based DAPT is theoretically more suitable for long‐term antiplatelet therapy among patients with MVD following DES implantation.

Given these, we designed the Dual Antiplatelet Therapy in Patients with Coronary Multi‐Vessel Disease (DAPT‐MVD) trial to evaluate whether extending DAPT with clopidogrel and aspirin for 12 months would improve the long‐term prognosis for MVD patients 12 months after DES implantation. The DAPT‐MVD trial aims to provide novel insights and robust clinical evidence for managing targeted patients. Given the possibility of increased bleeding risk, it is vital to prudently evaluate the preferable effect of prolonged DAPT [17, 18]. Hence, for MVD patients at 12 months after DES implantation, it is essential to weigh the beneficial effects of prolonged DAPT treatment against an increased bleeding risk.

## Methods

2

### Study Design and Population

2.1

The DAPT‐MVD study (ClinicalTrials. gov unique identifier NCT04624854) is a multicenter, open‐label, randomized, controlled trial aimed to evaluate the efficacy and safety of prolonged DAPT treatment in MVD patients beyond 12 months after DES implantation. The recruitment period for the study is planned to range from November 01, 2020, to the estimated primary completion date of April 30, 2024. A flow diagram of the patient recruitment process is shown in Figure 1. The primary hypothesis is that prolonged DAPT therapy will reduce the incidence of MACCE (including cardiovascular death, nonfatal myocardial infarction, or nonfatal stroke).

**Figure 1 clc70049-fig-0001:**
[figure not shown]
Study schema for DAPT‐MVD. *The time window is 12 ± 3 months; ^†^The treatment group received clopidogrel plus aspirin dual antiplatelet therapy within 12 months, while the control group received aspirin monotherapy within 12 months. Other treatments were given according to the clinical routine protocol; ^‡^The final follow‐up endpoint of the overall study is 12 months after the randomization of the last subject. d, Day; DES: Drug‐eluting stent; m, Month; MVD, Multivessel coronary artery disease; SCV, Site close‐out visit.

### The Participants‐Inclusion and Exclusion Criteria

2.2

After a median of 12‐month DAPT run‐in phase after DES implantation, a total of 8250 eligible patients recruited from ≥ 100 cardiology centers across China and randomized to continue a prolonged 12‐month DAPT treatment (75 mg clopidogrel plus 75–150 mg aspirin daily) or a monomer treatment (75–150 mg aspirin daily) until study completion. The enrolled subjects will have angiographically confirmed MVD with stenosis of ≥50% in more than two major epicardial coronary arteries and stenosis in the left main coronary artery ≤30% by visual assessment. Additional details of the inclusion and exclusion criteria are shown in Table 1.

**Table 1 clc70049-tbl-0001:** Inclusion/exclusion criteria.

Inclusion	Exclusion
Aged 18–75 years old (inclusive). Patients with MVD who underwent DES implantation for 12 months. Patients have been treated with aspirin and can tolerate aspirin at doses of 75–150 mg/day as maintenance therapy during the study period. Patients have signed informed consent.	Planned to use of ADP receptor blockers (eg, clopidogrel, ticagrelor, and ticlopidine), dipyridamole, or cilostazol. Contraindication to ADP receptor blockers or aspirin. Anticoagulants were planned to be used during the study period. Planned major cardiac or noncardiac surgery during the study period. Concomitant oral or intravenous therapy with CYP2C19 medium or strong inhibitors. Known severe liver disease (ALT/AST is three times above normal). Subjects with renal failure who required or anticipated dialysis during the study period. Platelet count < 50 × 10^9^/L. Patients with a. A history of intracranial bleeding or ischemic stroke at any time; b. A central nervous system tumor or intracranial vascular abnormality (e.g., aneurysm, arteriovenous malformation) at any time; c. Intracranial or spinal cord surgery within five years. Pregnancy or lactation or planned to be pregnant during the study period. Life expectancy < 1 year. In the investigator's opinion, any condition would make it unsafe or unsuitable for the patient to participate in this study (e.g., active malignancy other than squamous or basal cell skin cancer). Concern for the inability of the patient to comply with study procedures and/or follow‐up (e.g., alcohol or drug abuse). Participation in another clinical study and did not reach the major endpoint. Involvement in the planning and/or conduct of the study.

### Randomization and Treatment

2.3

After assessment for study eligibility requirements, patients will be assigned on a 1:1 basis to either the treatment group or the control group using a completely random method. Randomization will be conducted by a central computer network system. All eligible patients enrolled will receive 75–150 mg aspirin daily, and the treatment group will be recommended to take 75 mg clopidogrel daily for an additional 12 months from randomization. The subjects will receive experimental drug (the dose for 6 months, including the window period) at the research centers and their 6‐month follow‐up. As the study population is stable, no loading dose will be administered. Researchers may adjust the dose and regimen for antiplatelet medicines when adverse events occur in subjects. Other concomitant medications must be taken under the guidance. Any adjustment and distribution of study drugs should be recorded on the CRF form.

### Endpoints

2.4

A Clinical Events Committee (CEC) will evaluate all potential endpoints, with all committee members unaware of the trial group assignments. The primary endpoint is to determine whether extending DAPT with clopidogrel and aspirin for 12 months reduces the incidence of the composite efficacy endpoints of cardiovascular death, nonfatal MI, or nonfatal stroke (MACCEs) compared with aspirin monotherapy.

The secondary endpoints are to evaluate the effect of extending DAPT with clopidogrel and aspirin for 12 months on the incidence of all‐cause mortality, cardiovascular death, nonfatal MI, nonfatal stroke, net clinical adverse events (NACEs, including MACCEs and type 2–5 hemorrhage defined by Bleeding Academic Research Consortium [BARC]), cardiovascular death or hospitalization caused by cardiovascular or cerebrovascular thrombotic events (MI, stroke, emergency revascularization, unstable angina or transient ischemic attack (TIA), emergency revascularization, any repeat revascularization and definite/probable stent thrombosis (ST) individually in such patients.

The safety endpoints are to assess whether extending DAPT with clopidogrel and aspirin for 12 months increases the rate of clinically relevant bleeding events (BARC type 2–5) and the rate of major bleeding events (BARC type 3–5) relative to aspirin monotherapy.

### Follow‐Up

2.5

After randomization, participants will receive the assigned experimental drug treatment according to their group and have their treatment adherence and concomitant medication assessed at 1, 3, 6, 9, and 12 months of follow‐up. The experimental drug will be discontinued 12 months post‐enrollment. Participants may stop treatment at any time, and the experimental drug will also be discontinued if the researchers believe continued treatment poses potential risks. Then, after discontinuing the experimental drug 12 months post‐enrollment, subjects will continue to complete a 36‐month visit and the study close‐out visit (SVC) (12 months after the enrollment of the last patient). We will follow up on all participants’ potential endpoints and adverse events until death or the end of the follow‐up period.

### Sample Size Calculation

2.6

Based on data extracted from the PEGASUS‐TIMI 54 study, the expected annual rate of MACCEs is estimated to be 5% in the control arm [19]. It is anticipated that prolonged DAPT treatment in patients with MVD will reduce the target relative risk by 20% (i.e., the hazard ratio [treatment/control] is equal to 0.8) and the per‐year event rate by approximately 4% for the primary endpoint in those populations [20, 21]. Moreover, a two‐sided test is set at the 5% significance level, and 80% power is designed to reject the null hypothesis. The enrollment duration is estimated to be 24 months, and the follow‐up time is at least 12 months (with an expected median follow‐up time of 24 months). The enrollment progress in both groups was consistent, and eligible patients will be randomized on a 1:1 basis according to the protocol. Considering a 5% dropout rate and an expected noncompliance (switching groups) rate in those groups will be 3%. Therefore, the DAPT‐MVD trial is required to enroll at least 8250 subjects (4125 in each arm).

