## Limitations

5

This study has several limitations. First, the open‐label design introduces potential observational bias; however, this was mitigated by keeping the principal investigators blinded to group assignments, with data analysis conducted by an independent statistician. Second, the widespread transmission of COVID‐19 in China disrupted the trial recruitment process. To ensure adequate participant enrollment, the recruitment period was extended by an additional 18 months, and the number of study centers was increased. Third, there is a regional disparity in the trial population, with more participants from northern China than the south. However, this imbalance aligns with the higher prevalence of coronary artery disease in northern regions, which may enhance the generalizability of the findings.

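### The 80% power in Section 2.6 holds only if the hazard ratio of 0.8 persists after clopidogrel is stopped at month 12, and the protocol does not state that assumption

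*Protocol article*

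**What the plan says.** Section 2.6 of the protocol article gives these inputs:

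- Effect: prolonged DAPT will "reduce the target relative risk by 20% (i.e., the hazard ratio [treatment/control] is equal to 0.8", one constant value with no end date.
- Control arm: "the expected annual rate of MACCEs is estimated to be 5% in the control arm".
- Test: "a two‐sided test is set at the 5% significance level", and "80% power is designed to reject the null hypothesis".
- Time: "The enrollment duration is estimated to be 24 months", with follow-up of "at least 12 months (with an expected median follow‐up time of 24 months" months as the expected median.
- Allowances: 5% dropout and 3% switching between groups. The result is 8250 patients, 4125 per arm.

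Section 2.5 says: "The experimental drug will be discontinued 12 months" after enrolment. Section 2.3 and the note to Figure 1 also give a 12-month treatment period. Section 2.5 then follows endpoints through a 36-month visit and a close-out visit 12 months after the last patient is enrolled.

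Section 2.7 analyses time from randomization to the first primary event in the ITT set, by log-rank test and Cox model. It states no 12-month cut-off for efficacy. Bleeding, by contrast, is censored at the latest 7 days after the last dose.

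Section 5 adds that "the recruitment period was extended by an additional 18 months".

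**The concern.** The sample size paragraph credits the treatment arm with a 20% lower hazard for as long as patients are followed. The protocol takes that whole arm off clopidogrel at month 12. Under the planned accrual, 48-49% of the treatment arm's person-time falls after month 12; under 42 months of uniform accrual the share is 61-62%. The only allowance for departure from assigned treatment is 3% switching, which does not cover a planned stop in the whole arm.

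If the effect fades after the drug is stopped, later events carry little contrast and pull the overall hazard ratio towards 1. A drug that truly cut first-year events by 20% would then more likely than not give a non-significant primary result. It could be read as evidence against extended DAPT from a trial believed to have 80% power.

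**Working it through.** **1. Reproducing 8250.** The inputs are those of Section 2.6, with uniform accrual over 2 years, 1 further year of follow-up, and control hazard 0.05 per year (so 0.04 on treatment).

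- Events (Schoenfeld): 4 × (1.96 + 0.8416)² / (ln 0.8)² = 630.5.
- Event probability with follow-up uniform on 1 to 3 years: 1 − (e^−λ − e^−3λ)/(2λ). This is 0.0948 for λ = 0.05 and 0.0766 for λ = 0.04, mean 0.0857.
- N = 630.5 / 0.0857 = 7356. Dividing by 0.95 for dropout gives 7743, and by 0.97² for switching gives 8230, against 8250 stated.

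**2. The same calculation with a 12-month horizon.** The mean event probability is [(1 − e^−0.05) + (1 − e^−0.04)]/2 = (0.0488 + 0.0392)/2 = 0.0440. Then 630.5 / 0.0440 is about 14,300 patients, or about 16,000 after the same inflation. So 8250 rests on hazard ratio 0.8 also acting after month 12.

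**3. Power when the effect changes at month 12.** Let E1 and E2 be the events before and after month 12, with hazard ratios HR1 and HR2. Then

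z = (E1·|ln HR1| + E2·|ln HR2|) / (2·√(E1 + E2)), and power = Φ(z − 1.96).

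Example: planned accrual, no loss or switching, no carry-over.

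- E1 = 4125 × (0.0488 + 0.0392) = 363.
- E2, control arm: 4125 × (0.0948 − 0.0488) = 190.
- E2, treatment arm: 4125 × 0.9608 × (0.0460/0.9512) = 192. Total E2 = 382.
- Average log hazard ratio: 363 × (−0.2231)/745 = −0.1087, a hazard ratio of 0.90.
- z = 0.1087 × √745 / 2 = 1.48, so power = Φ(−0.48) = 32%.

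Loss is taken as 5% by 24 months. Switching of 3% each way turns 0.8 into (0.97 × 0.8 + 0.03)/(0.97 + 0.03 × 0.8) = 0.811. The 42-month accrual is 24 + 18 months. In each cell the first entry is with loss and switching, the second without.

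| Effect after month 12 | Accrual | E1 + E2 | Average HR | Power |
|---|---|---|---|---|
| None (HR 1.0) | 24 months | 358+366 / 363+382 | 0.90 / 0.90 | 29% / 32% |
| None (HR 1.0) | 42 months | 358+617 / 363+652 | 0.93 / 0.92 | 22% / 25% |
| Half (HR 0.9) | 24 months | 358+348 / 363+363 | 0.86 / 0.85 | 54% / 60% |
| Half (HR 0.9) | 42 months | 358+588 / 363+621 | 0.87 / 0.86 | 58% / 65% |
| Full (HR 0.8) | 24 months | 358+330 / 363+344 | 0.81 / 0.80 | 79% / 84% |
| Full (HR 0.8) | 42 months | 358+558 / 363+589 | 0.81 / 0.80 | 89% / 93% |
| Analysis cut at month 12 | either | 358 / 363 | 0.81 / 0.80 | 51% / 57% |

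Numerical integration of the log-rank drift and variance agrees to within about one percentage point.

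**4. Effect needed for 80% power.** Without carry-over, the year-1 hazard ratio must be about 0.61-0.64 with 24-month accrual, or about 0.56-0.58 with 42-month accrual. An analysis cut at month 12 detects about 0.72-0.74.

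**The case against.** The strongest reply is that the arithmetic is sound. The stated 8250 reproduces, and a constant hazard ratio can describe the strategy of 12 more months of DAPT over all follow-up. The Introduction gives the aim as better long-term prognosis, and an effect can outlast a drug. This stands in part. There is no slip in the calculation, and a reader who infers that the trial simply lacks its stated power goes further than the document allows, because it says nothing on persistence either way. What fails is the unconditional 80%: it depends on an assumption that the text neither states nor supports. If 0.8 was meant as the average over follow-up, then without carry-over the year-1 effect would have to be far larger than the 20% reduction anticipated.

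A reader might also infer that the longer recruitment can only harm power. It does not. It lowers power if the effect ends with the drug, but raises it if at least half persists.

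The analysis plan and the appendix are not shown and may set a time horizon. A 12-month horizon would make the no-carry-over figures of 22-32% inapplicable, but would itself give only 51-57%.

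The 42-month figures assume uniform accrual. The actual pattern is in Figure 2, which is not shown, and Section 5 says recruitment was disrupted and centres were added.

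Section 2.2 speaks of 12 months of DAPT and, in the same sentence, of treatment until study completion. That wording needs reconciling with Section 2.5, but it states no DAPT beyond 12 months.

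**Conclusion.** The point holds as a conditional one. The 80% power in Section 2.6 is reproduced only with a hazard ratio of 0.8 lasting through follow-up, while study clopidogrel ends at month 12 and the primary analysis has no stated 12-month cut-off. For the design as delivered, with about 42 months of accrual, power with loss and switching runs from 22% with no persistence, through 58% with half, to 89% with full persistence. The unstated assumption therefore decides whether the trial is well or poorly powered.

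These figures rest on a 5% annual control rate, 8250 patients, uniform accrual, constant hazards within each period, and a log-rank approximation under non-proportional hazards. The degree of persistence is not known from the document and is shown as a range. No single range should be quoted as the power of the design, since the 12-month figures belong to an analysis the article does not specify.

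**What to change.** In Section 2.6, replace the unconditional 80% with a statement that it holds only if the hazard ratio of 0.8 persists after month 12. Then give power and detectable hazard ratio for the delivered design (12 months of study drug, about 42 months of accrual, close-out 12 months after the last patient) under no, half and full persistence, and for a 12-month horizon. Use the actual accrual pattern in place of uniform accrual.

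No extra patients and no change to the analysis are requested. The cost is one rewritten paragraph and a less favourable stated power. The gain is that a non-significant result can be read against the power the trial really had.

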### Statistical Considerations

2.7

All potential endpoints will be adjudicated by the CEC and included in the efficacy analysis in the intention‐to‐treat (ITT) set, and a cross table of judgment results for the events will be listed. Subjects may develop more than one event during the study. For the composite endpoint, only the first event that occurs will be included in the time‐to‐event endpoint analysis. Unless otherwise specified, all statistical tests will be two‐sided and conducted at a 5% significance level. The detailed descriptions are summarized in Supporting Information S1: Appendix 1.

The primary endpoint will be the time from randomization to the first occurrence of its component. Initially, the Kaplan–Meier method will be employed to estimate the cumulative incidence of the primary endpoint and a log‐rank test will be conducted to compare survival curves between the treatment arms. Furthermore, a Cox proportional hazards model will be utilized to compare the hazard of having a primary outcome between the prolonged DAPT arm and control arm, providing a hazard ratio along with a 2‐sided 95% confidence interval (CI) to measure the treatment difference. In addition, the win‐ratio method for the hierarchical composite outcome will be performed as a supplementary analysis (Supporting Information S1: Appendix 1) [22]. All secondary time‐to‐event endpoints will be analyzed similarly as for the primary endpoint.

All safety analyzes will be based on the safety set. Descriptive statistical methods will be used to summarize the study drug exposure, the causes and times of study drug discontinuation, concomitant drugs, protocol deviations, clinical laboratory data, vital signs, and physical examination results in each treatment group. Patients not having suffered any bleeding event in the given category will be censored at the earliest of 7 days after the last dose of the study drug, death, last contact, or withdrawal of consent.

Covariate adjustment analysis aims to control for possible imbalances in the covariates, as listed in Table 2. The Cox model will be used for the covariate‐adjusted analysis, and the adjusted hazard ratio with its 95%CI will be estimated. In addition, subgroup analysis will be performed to assess the homogeneity of treatment effects across the categories of pre‐specified subgroup variables. Detailed statistical analyzes will be described in the statistical analysis plan. The trial results will be reported following the CONSORT guidelines for reporting randomized trials.

**Table 2 clc70049-tbl-0002:** List of covariates used in the covariate adjustment analysis.

Characteristics	Categories
Age	< 60, ≥ 60 year
Gender	Male, Female
Body mass index	< 28, ≥ 28 kg/m^2^
Diabetes	Yes, No
Hypertension	Yes, No
Hyperlipidemia	Yes, No
History of smoke	Yes, No
History of alcohol	Yes, No

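### Kaplan-Meier is named to estimate cumulative incidence of endpoints that non-component deaths preclude, so absolute risks will be slightly overstated

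*Protocol article*

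**What the plan says.** The protocol article, section 2.7 (Statistical Considerations), defines the primary endpoint as the time from randomization to the first component event. It then says of Kaplan-Meier that the "method will be employed to estimate the cumulative incidence of the primary endpoint". A log-rank test follows, and then a Cox model whose hazard ratio and 95% confidence interval measure the treatment difference. For secondary time-to-event outcomes, the "endpoints will be analyzed similarly as for the primary endpoint".

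Section 2.4 (Endpoints) limits the primary composite to cardiovascular death, nonfatal MI and nonfatal stroke. The secondary endpoints include these components singly, repeat and emergency revascularization, stent thrombosis, all-cause mortality and a net clinical composite.

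Bleeding is a safety endpoint. Section 2.7 names no estimator for it, but says that patients without a bleed are "censored at the earliest of 7 days after the last dose of the study drug, death, last contact, or withdrawal of consent".

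The article does not mention competing events or a competing-risk estimator. It refers further detail to Appendix 1 and to the statistical analysis plan, neither of which is at hand.

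**The concern.** Cumulative incidence is the proportion of patients who will have had the event by a given time. A patient who dies of a non-cardiovascular cause can no longer have a MACCE. Kaplan-Meier treats that patient as censored, which assumes that an event could still occur later at the same rate as in patients still at risk. One minus Kaplan-Meier therefore never falls below the cumulative incidence, and it exceeds it once competing deaths occur. The named estimator and the named quantity do not match.

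The competing event depends on the endpoint:
- MACCE and cardiovascular death: non-cardiovascular death competes.
- Nonfatal MI, nonfatal stroke, stent thrombosis and revascularization taken singly: any death that is not itself the event competes.
- Net clinical composite: only deaths that are neither cardiovascular nor due to bleeding compete.
- All-cause mortality: nothing competes, and Kaplan-Meier is correct.

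At stake are the absolute risks read from the curves. The Introduction and Conclusion present the trial as weighing ischaemic benefit against bleeding, and readers will do that weighing partly on absolute risks.

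**Working it through.** **The plan's own figure.** The article states no cumulative incidence, so the only figure to reproduce is the sample size.
- Events for HR 0.8, two-sided 5%, 80% power: 4 × (1.960 + 0.842)² / (ln 0.8)² = 631.
- Event probability with uniform 24-month accrual plus 12 months: 1 − (e^(−λ) − e^(−3λ)) / (2λ). This gives 9.48% for λ = 0.05 and 7.66% for λ = 0.04, mean 8.57%.
- 631 / 0.0857 = 7362; / 0.95 for dropout = 7749; / 0.97² for switching = 8236, against the stated 8250.

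No curve estimator enters this calculation, so the point does not touch the sample size.

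**Inputs for the competing-risk check**
- Control MACCE rate, section 2.6: "the expected annual rate of MACCEs is estimated to be 5% in the control arm". As a hazard, λ = −ln(0.95) = 0.0513 per year.
- Treatment hazard at HR 0.8 (section 2.6): 0.8 × 0.0513 = 0.0410.
- Non-cardiovascular death hazard c: not given anywhere. Assumed 0.005 to 0.02 per year, constant and equal in both arms.

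**Formulas** (constant hazards)
- One minus Kaplan-Meier (KM): 1 − e^(−λt)
- True cumulative incidence, the Aalen-Johansen (AJ) target: λ/(λ + c) × (1 − e^(−(λ + c)t))

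**Control arm**

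| Years | KM | AJ, c = 0.005 | AJ, c = 0.02 | KM too high by |
|---|---|---|---|---|
| 1 | 5.00% | 4.99% | 4.95% | 0.01-0.05 points |
| 2 | 9.75% | 9.70% | 9.56% | 0.05-0.19 points |
| 3 | 14.26% | 14.16% | 13.85% | 0.10-0.41 points |

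Reading 5% as the hazard itself (λ = 0.05) hardly changes the gap: 0.05-0.19 points at 2 years and 0.10-0.40 at 3 years.

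**Between arms at 3 years**
- KM: 14.26 − 11.58 = 2.68 points, NNT 37.3.
- AJ: 2.66 points (c = 0.005) to 2.60 points (c = 0.02), NNT 37.6 to 38.4.
- The KM difference is too large by 0.02-0.08 points, and the KM number needed to treat is correspondingly too small.
- Sampling standard error of that difference with 4125 per arm and no censoring: √[(0.1426 × 0.8574 + 0.1158 × 0.8842) / 4125] = 0.74 points. The bias is at most about a tenth of one standard error.

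**Dependence on equal death rates.** If c were 0.005 in the control arm and 0.01 in the treatment arm, the 3-year AJ difference would be 14.16 − 11.41 = 2.75 points. Kaplan-Meier would then be about 0.07 points too low. The direction for a single arm is fixed, but the direction for the difference is not.

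**Components.** The Discussion cites cumulative risks of 3.1% for all-cause death, 1.9% for MI and 0.7% for stroke, without a time horizon. If these are taken as 1-year risks and every death competes (both assumptions), the 2-year figures are 3.76% by KM against 3.65% for MI, and 1.40% against 1.35% for stroke. Each is about 3.2% too high in relative terms.

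**The case against.** The strongest reply is that nothing the trial will be judged on changes. Section 2.7 measures the treatment difference by the hazard ratio and tests it by log-rank. Both remain valid as cause-specific comparisons when competing deaths are censored. No risk difference or number needed to treat appears among the planned analyses. All of this stands and keeps the point minor.

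A second reply is that Appendix 1 or the statistical analysis plan may handle competing deaths. That also stands: the article's silence does not show that the plan has no competing-risk analysis. But the article does name an estimator for a named quantity, and that sentence needs correcting whatever the other documents add.

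Third, the 2% per year upper limit has no support in the documents. Patients are at most 75, the mean age is 60.5, and Table 1 excludes a life expectancy under 1 year. The low end of the range, about 0.1 points at 3 years, is the more plausible.

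A reader might infer more than the documents support:
- **That the bias approaches a full point.** With first enrolment in October 2020, enrolment completed by April 2024 and close-out 12 months after the last patient, the earliest patients could reach about 54 months. The same formulas there give 20.61% against 19.75-20.39%. Only the earliest enrolled get that far, and the planned median follow-up is 24 months.
- **That numbers needed to treat are inflated.** The number is the reciprocal of the risk difference, so when the difference is overstated it comes out too small.
- **That bleeding is affected in the same way.** The rule about similar analysis covers secondary endpoints, and no Kaplan-Meier estimator is stated for bleeding. Censoring 7 days after the last dose of a 12-month treatment also limits the horizon to about one year.

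**Conclusion.** The point holds as a minor one. Section 2.7 names Kaplan-Meier for the cumulative incidence of MACCE and, by extension, of the secondary time-to-event endpoints, where non-component deaths compete. Absolute risks in each arm will be slightly too high, by amounts that grow with follow-up and are negligible at 12 months. The between-arm contrast barely moves. No conclusion about the validity of the primary test, the hazard ratio or the trial size follows.

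The sizes rest on constant hazards, the article's 5% annual control rate and HR 0.8, and an assumed non-cardiovascular death rate. The direction stated for the risk difference also needs that rate to be similar in both arms. The component figures rest further on reading the Discussion's risks as annual.

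**What to change.** In section 2.7, or in the statistical analysis plan with the article's sentence corrected to match:
- Estimate and plot cumulative incidence with the Aalen-Johansen estimator. For each endpoint, treat deaths that are not a component of it as competing events.
- Keep the log-rank test and Cox model, and label them as cause-specific analyses.
- Keep Kaplan-Meier for all-cause mortality.
- If cumulative bleeding incidence is reported, treat death as a competing event there rather than as a reason for censoring.

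The cost is about one line of text and a different software call. Cause of death is already needed for the primary endpoint, so no new data are required. The design, the primary test and the sample size do not change.
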